## Materials and Methods

### Participants

Trial participants are community-living elderly aged 60 years and above. Some are participants from two previous studies on healthy aging (approval number: NUS 1351 and NUS 2501) who had consented to be contacted for future research, with additional participants recruited through door-to-door visits. Screening is done by trained research nurses and psychologists. Participants are included if they presented self-reported subjective cognitive complaints, objective cognitive impairment based on neuropsychological test scores (age- and education-standardized Z-scores in the range of 0 to −1.5 for at least five tests, out of 10) or at least two risk factors of dementia (family history of dementia, physical inactivity, low social engagement, heart disease, transient ischemia attack, diabetes, head injury, living alone and depressive symptoms), but are not demented (Clinical Dementia Rating global score = 0). Exclusion criteria are conditions preventing effective engagement in the intervention, such as: terminal illness, stroke, aphasia and marked hearing impairment, as well as participation in another interventional study.

Eligible participants are given sufficient information about the study and provide their informed consent prior to a screening assessment. Results of the screening also act as a baseline measurement. Recruitment will proceed until a total of 360 participants is reached.

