### Randomization

Following informed consent, randomization into intervention or control arm is performed with a 1:1 allocation ratio. Balanced treatment assignments will be achieved using permuted block randomization. The block length is determined by an independent statistician and is not made known to the clinical investigators or site personnel. Opaque, sequentially numbered and sealed envelopes are prepared for the randomization process. Authorized site personnel open the randomization envelopes in sequential order to determine the participant’s treatment arm and the identification number to be used for that participant.

Participants randomized to the intervention arm participate in choral singing for 2 years while participants in the control arm take part in general health education and group activities.

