### Assessments and Outcome Measures

A comprehensive assessment protocol with cognitive and psychological measures, blood and urine biomarkers and brain MRI measures has been designed for this study. Participants undergo questionnaire-based interviews, cognitive testing, clinical assessments, specimen collection and MRI prior to, during and at the end of the intervention (Table 1). Assessors at each follow-up are blind to group allocation.

**Table 1 T1:** Measurements and visit schedules.

	Measurement	Baseline	6 months	1 year	2 year
1	Social, demographic and lifestyle data	√			
2	Medical conditions and medications	√			
3	Mini mental state examination (MMSE)	√	√	√	√
4	Subjective memory and cognitive complaint	√		√	√
5	Neuropsychological testing/assessment	√		√	√
6	Clinical dementia rating (CDR)	√		√	√
7	Neuropsychiatric inventory (NPI)	√		√	√
8	Activities of daily living (ADL)	√		√	√
9	Instrumental activities of daily living (IADL)	√		√	√
10	Pittsburgh sleep quality index (PSQI)	√	√	√	√
11	Geriatric depression scale (GDS-15)	√	√	√	√
12	Geriatric anxiety inventory (GAI)	√	√	√	√
13	Perceived stress scale (PSS)	√	√	√	√
14	Rhythm experiment	√		√	√
15	The social cognition and behavior assessment	√		√	√
16	Gold-MSI	√			√
17	Venous blood sample collection	√		√	√
18	Urine sample collection	√	√	√	√
19	Brain MRI, blood pressures, pulse rates	√		√	√

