## Methods of Analysis

CCTS at each follow-up visit, absolute changes from baseline and percentage changes from baseline during the intervention period will be compared between the two arms using Student’s *t*-test and repeated-measures analysis of variance (ANOVA). Following this, a linear mixed-effects model will be conducted to examine the main effect of time and group allocation, and the interaction between time and group allocation, adjusting for potential confounders where necessary. Fisher’s exact tests will be used to compare the difference in dichotomous outcome measures such as cognitive decline, defined as the one or more points in MMSE score, between the two arms. Multiple logistic regressions with adjustment for important baseline characteristics will be conducted in the event of important baseline non-comparability. Statistical analysis will be conducted using SPSS, Stata or R. Interim analysis will be conducted for the first group of participants using data collected at 6 months, 12 months and 24 months, respectively.

The statistical analysis for DNA methylation will be performed using a modified version of the CPACOR pipeline to eliminate potential confounders such as bisulfite conversion, batch effect, and white blood cell composition (Lehne et al., 2015). Marker intensities will be normalized by quantile normalization. We will use the epigenome-wide methylation scores to impute white blood cell subsets using the Houseman method (Houseman et al., 2014). A principal components analysis will also be performed to quantify latent structure in the data, including batch effects. Single-marker tests using logistic regression will be used to examine the association of each autosomal CpG site with condition (choral singing/control), adjusted for age and sex. We will also calculate the methylation age using the 353 CpG sites previously identified (Horvath, 2013). Principal components from intensity values of Infinium control probes, which accounts for various technical parameters such as bisulfite conversion batch, will also be included as covariates in the regression models. Finally, the association results will be adjusted for genomic control inflation factor.

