## Progress

Starting from July 2015, 404 community-living seniors were invited to the screening. Of these, 197 participated and 93 were recruited. The target of identifying and randomizing the first group of participants was achieved in October 2015. The intervention was initialized on schedule with the choral singing intervention starting on 29 October 2015 and the control intervention starting on 4 November 2015. More participants will be recruited through 2017 and 2018 until the target of 360 is met. Final data collection is expected to take place in February 2020 (see Figure 2 for participant flowchart; Schulz et al., 2010). Baseline measurements, MRI scans, bio-sampling and follow-up measurements at 6 months and 1 year after the start of the intervention have been collected for the first batch of participants. Electronic data entry and processing are ongoing. The baseline characteristics of the first group of participants are summarized in Table 3.

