## Discussion

The study investigates whether a choral singing intervention can prevent or delay cognitive impairment in an older population at increased risk of cognitive decline. Although theoretically plausible, its effectiveness has not been studied scientifically in an RCT. In this study, participants are randomly allocated, with clinical investigators and assessors at each follow-up blinded to the group allocation. The sample size is suitably large and the relatively long intervention period compared to previous singing studies allows for analyzing more long-term effects and increases the chances for the intervention to show efficacy. The use of an active control arm rather than an empty control or “usual care” will distinguish the effect of choral singing from the benefit of activities in a group context. This study thus provides a rigorous test of choral singing’s effectiveness in preventing cognitive decline. Analysing patterns of change over time with a detailed biomarker and MRI assessment battery will allow investigation into potential mechanisms behind the effects of the intervention.

A comprehensive set of measures was designed to encompass the wide range of cognitive, emotional and physical effects of choral singing. However, the many secondary outcome measures taken at multiple time points open the study up to the problem of multiple comparisons problem. Statistical adjustments for the number of comparisons will be made. A multidomain composite cognition score not only reduces the need for multiple comparisons, but is optimal for detecting very early cognitive changes in non-impaired individuals as it is more sensitive to changes than its individual components (Coley et al., 2016; Mormino et al., 2017).

The relative lack of diversity in the sample is a potential limitation. Thus far, participants are predominantly ethnic Chinese and women. Women tend to report stronger well-being effects from choral singing compared to men (Sandgren, 2009), possibly inflating any positive effects of the intervention. The study is also specific to Singaporean older adults, reducing the generalizability of findings. However, the research on choral singing conducted around the world suggests that its benefits transcend culture and countries (Clift and Hancox, 2010).

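### Interim analyses of the first 93 participants fall while the trial is still running and have no stated purpose or claim rule, and the CCTS comparison at every follow-up visit cannot be done at 6 months

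*Protocol article*

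**What the plan says.** All references are to the protocol article.

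- **Interim looks.** Methods of Analysis: "Interim analysis will be conducted for the first group of participants using data collected at 6 months, 12 months and 24 months, respectively". The sentence names no outcome, purpose or threshold.
- **Who is in the first group.** Progress: "Of these, 197 participated and 93 were recruited". Table 3 splits them 47 to choral singing and 46 to control.
- **Recruitment continues.** Participants section: "Recruitment will proceed until a total of 360 participants is reached". Progress: "More participants will be recruited through 2017 and 2018 until the target of 360 is met", and "Final data collection is expected to take place in February 2020".
- **How an effect is recognised.** Methods of Analysis applies a linear mixed-effects model to every data set and takes a significant group × time interaction as showing an effect of singing. No exception is made for interim data.
- **Multiplicity.** The Discussion promises adjustment, but the problem it describes is the number of secondary outcomes and time points. It presents the composite score as reducing the need for adjustment.
- **Blinding.** The Discussion describes the trial as run "with clinical investigators and assessors at each follow-up blinded to the group allocation". The assessment section says the same of assessors. Neither statement mentions interim results.
- **6-month visit.** Frequency of Assessments lists 6 months as a follow-up visit, and Methods of Analysis compares the CCTS between arms at every follow-up visit. In Table 1 the row "Neuropsychological testing/assessment", which supplies the CCTS, is ticked at baseline, 1 year and 2 years only.

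**The concern.** Two separate things are at issue.

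The first is the status of the three looks. The paragraph containing the interim sentence otherwise sets out comparisons of the two arms, so a comparative interim is the natural reading, though it is an inference. If those comparisons use the CCTS, and a significant result may be reported as efficacy, the primary question is tested more than once, partly on the same people. Whether or not a claim is made, arm-level results would become available while the other 267 participants (360 − 93) are still being enrolled, encouraged to attend and tested. The control sessions are run by a study investigator and project nurses, and the research team contacts absentees in both arms. Staff who knew which arm was ahead in the first cohort could act on it without intending to.

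The second is a plain mismatch: the article plans a CCTS comparison at a visit where the tests that make up the CCTS are not given.

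**Working it through.** **Figures in the plan.** The article gives no alpha, power or interim boundary, so there is no stated error rate to reproduce. The two-sided 0.05 and the visit correlations used below are assumptions.

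**Timing.** The sessions began on 29 October 2015 (singing) and 4 November 2015 (control). Adding 6, 12 and 24 months puts the looks at about April/May 2016, October/November 2016 and October/November 2017. Recruitment runs through 2018, so all three precede its end. The abstract dates the start of screening one year later; moving the looks by a year puts the last at about October/November 2018, still within the recruitment period.

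**Overlap.** First-cohort share f = 93/360 = 0.258.

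**Correlation of the tests.** With a common 24-month contrast, Z_final = √f · Z_first,24 + √(1 − f) · Z_later. Hence:

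- corr(Z_first,24, Z_final) = √0.258 = 0.508
- corr(Z_first,12, Z_first,24) = ρ, assumed 0.3 to 0.9
- corr(Z_first,12, Z_final) = 0.508ρ

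**Overall false-positive rate if any look can support a claim.** This is P(at least one |Z| > 1.96) under no effect, from 4 million multivariate normal draws:

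| Looks on the CCTS | ρ | Overall rate |
|---|---|---|
| First cohort 24 months, final | not needed | 9.1% |
| First cohort 12 and 24 months, final | 0.3 | 13.3% |
| same | 0.5 | 12.9% |
| same | 0.7 | 12.1% |
| same | 0.9 | 10.9% |

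For reference, three independent tests give 1 − 0.95³ = 14.3%.

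The 6-month look is left out because no CCTS exists then. The final test is treated as a single 24-month contrast; the article's group × time test over several visits was not simulated, so these rates are approximate for it.

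**If no interim claim or stop is possible.** Only the final test counts, and it keeps its nominal level.

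**With the proposed threshold.** Testing the first cohort at p<0.001 (|Z| > 3.29) at 12 and 24 months and the final at 0.05 gives 5.1% to 5.2% over the same range of ρ.

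**What an early comparison could show.** The detectable standardized difference at 80% power is (1.96 + 0.84) × √(2/n) with n per arm. With n = 46.5 this is 0.58; with n = 180 it is 0.30. At a true difference of 0.30 SD, chosen only for scale, power is about 30% in the first cohort and 81% in the full trial.

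**6 months.** Table 1 ticks MMSE, PSQI, GDS-15, GAI, PSS and urine at that visit. The neuropsychological battery is not ticked, so the CCTS cannot be computed. Table 1, Frequency of Assessments and the CCTS sentence in Methods of Analysis cannot all stand as written.

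**The case against.** The strongest reply is that this is a condensed article. Interim boundaries and rules on who sees results are commonly left to the full protocol or the analysis plan, neither of which is shown. That stands: their absence here is not in itself an error, and they may exist.

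Three stronger readings are tempting, and the article does not support them.

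- *The trial runs at an 11–13% false-positive rate.* No stopping rule or early efficacy claim is stated, recruitment is to continue to 360, and the stated aim is 2-year efficacy. The figure needs a rule that lets any look count. The mixed-model sentence leaves room for such a claim but does not assert it for the interim.
- *There is no blinding protection.* Assessor and investigator blinding are stated, and allocation uses sealed opaque envelopes with an undisclosed block length. Aggregate first-cohort results would not tell an assessor any later participant's arm. What the article leaves open is narrower: who sees the interim results.
- *The 6-month interim cannot be carried out.* The interim sentence does not name the CCTS. That look can use the MMSE and the other scales collected then. The conflict lies with the sentence comparing the CCTS at every follow-up visit.

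The reply does not reach two points. The multiplicity statement, as worded, does not cover repeated looks at the primary outcome. And no unseen document reconciles the article's CCTS sentence with its own Table 1.

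**Conclusion.** The point holds in a limited form. The article commits to three looks at 26% of the sample during recruitment and re-uses those participants at the end, and the safeguards it states are not directed at those looks. That the looks compare arms is a reasonable inference, not a stated fact.

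The inflation is conditional. It is about 9%, or 11–13% if the 12-month look also counts, only if a first-cohort CCTS result can support a claim or stop the trial, with 0.05 per look and visit correlations of 0.3 to 0.9 assumed. Otherwise it is nil, and the concern is confined to arm-level results influencing conduct.

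The 6-month CCTS mismatch is firm and needs no assumption. Both parts merit a change, mainly of wording.

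**What to change.** 1. State that first-cohort interim reports are pooled across arms (attendance, retention, data quality) until the 2-year CCTS data are locked. If a comparative look is kept, have the independent statistician run it at p<0.001, withhold the results from investigators and assessors, and keep the final test at 0.05. State that no efficacy claim will be made from the first cohort unless that threshold is met. Other boundaries would also serve; this one is simple and leaves the final test almost untouched. If the full protocol already holds such rules, a sentence pointing to them is enough.
2. Limit CCTS comparisons to 1 and 2 years, and name the 6-month outcomes as MMSE, PSQI, GDS-15, GAI, PSS and urine markers.

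The cost is a few sentences. The real downside is that between-arm results from the first cohort could not be published early; with about 30% power at 0.30 SD, little reliable information is given up.

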The levels of stable biomarkers of oxidative damage will give an indication of the overall oxidative state of the individual. As psychological stress and cognitive dysfunction are associated with increased oxidative damage, we hypothesize that the levels of these peripheral oxidative damage biomarkers will decrease in the intervention group relative to baseline and the control group. We postulate that the intervention would affect the senescence profile of immune cells from participants including their secretory profile (cytokine measurement and PD1 expression) and the replicative senescent status (proliferation and CD57 expression). Inflammatory monocytes (CD16+) were shown to be up-regulated in aging and in cases of inflammatory conditions. The impact of the intervention on the overall pro-inflammatory profile should be noticed in either the lymphoid or myeloid compartment.

Epigenome-wide methylation data will be generated for the samples using the state-of-the-art Illumina Infinium MethylationEPIC BeadChip (Pidsley et al., 2016). The array covers over 850,000 methylation sites per sample at single-CpG site resolution, providing unparalleled coverage of CpG islands, RefSeq genes, ENCODE open chromatin, ENCODE transcription factor binding sites, and FANTOM5 enhancers, as well as regions identified by the ENCODE project as potential enhancers.

DNA methylation will be quantified in the baseline DNA samples from venous blood. Bisulfite conversion of genomic DNA will be done using the EZ DNA Methylation kit, which requires ~500 ng of input DNA. The methylation profiling will be repeated for DNA samples from venous blood collected at the 2 year time point. We expect methylation age (calculated from the 353 CpG sites) to be lower in the participants assigned to the choral singing group relative to the control group as choral singing is expected to be associated with healthy aging.

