MRI images obtained from baseline and follow-up visits will be used to track relevant features such as hippocampal, whole-brain, total cerebral volume and annualized rate of atrophy; total ventricular volume, temporal horn volume; white matter volume and shape; fractional anisotropy and mean diffusivity and radial diffusivity; and the number of white matter lesions and cerebral micro-bleeds. Software such as FreeSurfer and BrainVoyager will be used in image processing and analysis. Functional connectivity analysis will be conducted using group ICA to track changes in networks such as the default mode network and the social brain network. As the face-name paired associates and melodic memory tasks are expected to involve episodic memory, the hippocampus is an *a priori* area of interest. Hemodynamic response function (HRF) time-locked to the presentation of stimuli will be extracted and analyzed.

For all data sets, a linear mixed-effects model will be used to analyze changes in mean responses over time for each group and the interaction term between group allocation and the time variable. A significant group × time interaction will indicate an effect of the choral singing intervention, following which appropriate *post hoc* tests can be done.

Intention-to-treat and per protocol analyses will be conducted. Compliance is monitored. Sensitivity analysis will be conducted by excluding subjects whose compliance (attendance) rate is below a specific cutoff point.

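### The per-CpG methylation test names no time point and no baseline methylation term, and it is not reconciled with the mixed model stated for all data sets

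*Protocol article*

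**What the plan says.** The Biomarkers section of the protocol article sets two methylation measurements per participant: "DNA methylation will be quantified in the baseline DNA samples from venous blood", and "The methylation profiling will be repeated for DNA samples from venous blood collected at the 2 year time point". The array covers more than 850,000 sites.

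The Methods of Analysis section then gives the site-level test: "logistic regression will be used to examine the association of each autosomal CpG site with condition (choral singing/control), adjusted for age and sex". Principal components of the control-probe intensities "will also be included as covariates in the regression models". The pipeline is meant to "eliminate potential confounders such as bisulfite conversion, batch effect, and white blood cell composition", and the methylation scores are used "to impute white blood cell subsets using the Houseman method". The text does not say whether the imputed fractions become covariates, or from which visit. It names no time point for the CpG value, no baseline methylation term and no time term.

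After the imaging methods, the same section states a general rule: "For all data sets, a linear mixed-effects model will be used to analyze changes in mean responses over time". It adds that a significant interaction of group and time will be taken as an effect of the intervention.

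**The concern.** The article describes two different analyses of the same repeated measurement. In one, the randomized arm is the outcome and a single methylation value is the predictor. In the other, the measurement is the outcome and the test is the group-by-time interaction. They have different outcomes, different tests and, as shown below, different power, and the text does not say which decides whether methylation responded to singing.

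The single-site model has the form of a case-control analysis. What it tests depends on the unstated time point. On baseline samples it can detect only chance imbalance between the arms. On 2-year samples it is a valid randomized comparison that leaves the paired baseline value unused. For the primary cognitive score the same section does name change from baseline; for methylation it does not. At stake is precision where the multiplicity burden is heaviest.

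Cell composition raises a related question. At 2 years it is a post-randomization variable, and the Biomarkers section expects an immune response: "We postulate that the intervention would affect the senescence profile of immune cells from participants". If 2-year fractions were used as covariates, part of an effect acting through immune cells could be adjusted away.

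**Working it through.** **Plan's own figure.** There is none to reproduce. The article gives no power, effect size, alpha or correlation for methylation.

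**Inputs from the article.** 360 participants (Participants) allocated 1:1 (Randomization), so n = 180 per arm if all supply both samples; over 850,000 sites (Biomarkers), rounded to 850,000. The autosomal count is not given.

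**Assumptions.**
- Bonferroni alpha, two-sided: 0.05/850,000 = 5.88 × 10⁻⁸, critical z = 5.42. The Discussion promises adjustment for multiple comparisons without naming a method.
- Effect d = 0.5 SD of the 2-year value.
- Baseline-to-2-year correlation r from 0.2 to 0.9.

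**Formulas (normal approximation).** Power = Φ( d / [√(2/n) × s] − 5.42 ), with √(2/180) = 0.1054 and residual SD s as follows:
- 2-year value alone: s = 1.
- Baseline as covariate: s = √(1 − r²).
- Unconstrained group-by-time interaction with two visits, which is a comparison of change scores: s = √(2(1 − r)).

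The share of information lost by omitting baseline is 1 − (1 − r²) = r².

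**Numbers put in, d = 0.5.** For the 2-year value alone, 0.5/0.1054 = 4.74, and Φ(4.74 − 5.42) = 25%. With baseline at r = 0.5, s = 0.866, 4.74/0.866 = 5.48, and Φ(0.06) = 52%. With the interaction at r = 0.3, s = 1.183, 4.74/1.183 = 4.01, and Φ(−1.41) = 8%.

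| r | Information lost (r²) | Power, 2-year value alone | Power, baseline covariate | Power, unconstrained interaction |
|---|---|---|---|---|
| 0.2 | 4% | 25% | 28% | 5% |
| 0.3 | 9% | 25% | 33% | 8% |
| 0.5 | 25% | 25% | 52% | 25% |
| 0.7 | 49% | 25% | 89% | 76% |
| 0.8 | 64% | 25% | 99% | 98% |

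At r = 0.9 the information lost is 81%.

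**Smallest effect detectable with 80% power.** (5.42 + 0.84) × 0.1054 × s gives 0.66 SD for the 2-year value alone. With baseline as covariate it is 0.65 (r = 0.2), 0.57 (0.5), 0.47 (0.7) and 0.29 (0.9). With the unconstrained interaction it is 0.84, 0.66, 0.51 and 0.30.

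**Where the interaction falls behind.** 2(1 − r) exceeds 1 whenever r < 0.5, so at such sites the interaction has less power than the 2-year value alone. The baseline-covariate model is never worse than the 2-year value alone, apart from one degree of freedom.

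**Sensitivity to d.** At 0.65 SD, power is 77% without baseline and 96% with it at r = 0.5. At 0.8 SD it is already 98% without baseline. The gain therefore matters most for moderate effects at stable sites.

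**Check on the logistic form.** In 600 simulated data sets per r, with an effect of 0.4 SD, the mean logistic z without and with a baseline term was 3.67 and 3.74 (r = 0.2), 3.63 and 4.13 (0.5), and 3.64 and 5.72 (0.8). The missing baseline term, not the logistic link, accounts for most of the loss.

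**The case against.** The strongest reply is that the article is a condensed account. It does not state the time point of the CpG value, so a change value is not ruled out, and the full protocol or analysis plan may settle it. The article also layers analyses elsewhere: for the cognitive score it lists t-tests, repeated-measures ANOVA and then a mixed model. A site-level screen followed by a mixed model need not be a contradiction, and if the mixed model governs, the baseline samples are used. The general rule also follows the imaging paragraph, so some may read it as meant for imaging data.

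This limits the point but does not remove it. The article does fix the model, the outcome and the covariates of the single-site test, so this is more than detail left elsewhere. The rule is worded for every data set, and nothing says which analysis decides. Letting the mixed model govern is also not a safe default, because its unconstrained interaction loses power at sites with r below 0.5.

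Some stronger readings are tempting and are not supported:
- A reader might infer that the model adjusts for age and sex alone. Control-probe components are also covariates.
- A reader might infer that most of the epigenome-wide power is wasted. The documents give neither r nor d, and more than half of the information is lost only if r exceeds 0.71 (√0.5).
- A reader might infer that methylation age is analysed without baseline. The article says how it is calculated and which direction is expected, but ties no baseline-free model to it.
- A reader might infer that only cell-adjusted results will be shown, hiding an immune effect. The article does not say so, and immune markers are measured separately.

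**Conclusion.** The point holds as a matter of efficiency and consistency. The single-site test lacks a stated time point and a baseline methylation term, and it is not reconciled with the general mixed model. If it is run on 2-year samples, randomization keeps it valid; there is no bias, and the primary cognitive outcome is untouched.

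The size depends on r, which is assumed throughout. The cost of omitting baseline is negligible at sites where methylation is poorly correlated over 2 years and large where it is stable. The power figures rest further on the assumed d, on Bonferroni control at 0.05/850,000 and on 180 complete pairs per arm. With dropout all of them fall, but r² as the share of information lost does not change. The cell-composition point is conditional: it applies only if imputed fractions enter as covariates and are taken from the 2-year samples.

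**What to change.** State one governing model for the site-level test: methylation at 2 years as the outcome, with arm, baseline methylation at that site, age, sex and control-probe components as predictors. A mixed model on both visits is an acceptable alternative if the baseline means are constrained equal across arms. An unconstrained group-by-time interaction should not be treated as equivalent. Say explicitly that this model takes the place of the general mixed-model rule for the methylation data.

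If imputed cell fractions are used as covariates, take them from baseline for the total effect of the intervention. Show any version adjusted for 2-year fractions beside it, labelled as adjusted for a post-randomization variable.

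The cost is a change of analysis wording, one degree of freedom per site and some computing. No new samples are needed. The covariate model is restricted to participants with both samples; the constrained mixed model retains the others.
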